### Data Management

Investigators collect the information in a validated electronic data system managed by a contract research organization (Advice Pharma Group Srl). The contract research organization is responsible for checking the completeness of the data, monitoring the quality of the data, identifying any extreme values (outliers), and storing the information securely according to legal requirements. Access to the data is strictly limited to authorized personnel only, and individual patient information is deidentified prior to analysis.

### End Points

The primary objective of the study is to investigate menstrual cycle control by evaluating breakthrough bleeding (ie, bleeding or spotting between the cyclically regular onset of menses) during the use of the monophasic NGM/EE 0.25/0.035 mg COC. This is measured by calculating the intermenstrual bleeding or spotting occurrence rate at the sixth cycle and comparing this with the rate at baseline.

Secondary outcomes include the change from baseline at visits 2 and 3 in other parameters of cycle control (frequency, duration, regularity, participant-determined flow volume, and unscheduled bleeding), GAGS score, POMS, FSFI, and dysmenorrhea severity based on the VAS rating. Adherence and contraceptive failure rate over the 6-month study period are also secondary outcomes, as are changes from baseline in the metabolic, hormonal, or coagulation parameters in the subgroup of participants from Genoa. Adherence is being evaluated as a percentage of tablets taken, based on the medication returned by participants at each visit. Contraception failure is defined as the proportion of women who become pregnant during the 6-month study period. The reasons for any contraception failure will be identified and listed (eg, discontinuation or poor adherence).

### Safety Outcomes

AEs, including any serious adverse events (SAEs), are the key safety outcome. An AE can be any unfavorable and unintended sign (including an abnormal laboratory finding), symptom, or disease temporally associated with the use of NGM/EE 0.25/0.035 mg, whether considered related or not. This may include exacerbation of existing conditions, suspected drug-drug interactions, or clinically significant abnormal laboratory findings, although an abnormal laboratory finding may not be considered as an AE if there is no change compared to baseline values. Abnormal laboratory values or test results represent an AE only if they induce clinical signs or symptoms, are clinically significant, or require therapy. An SAE is any AE that results in death, is life-threatening, requires inpatient hospitalization or prolongation of an existing hospital stay, results in persistent or significant disability or incapacity, or results in a congenital anomaly or birth defect. Other medical events that may jeopardize the participant or may require a medical or surgical intervention to prevent an SAE are also considered to be serious.

Investigators will record any AEs or SAEs in a case report form, with a description of the event, date of occurrence, an assessment of its severity and potential relationship to NGM/EE 0.25/0.035 mg, and the outcome (including date of resolution). If there is at least a reasonable possibility that NGM/EE 0.25/0.035 mg is the cause of the AE (ie, that causality cannot be ruled out), the AE will be considered as an adverse drug reaction. The severity of the AE will be rated as mild (transient and generally not interfering with usual activities), moderate (sufficiently discomforting to interfere with usual activities), or severe (inability to perform usual activities). AEs of special interest in this study are hypertension, arterial thromboembolism, myocardial infarction, stroke, transient ischemic attacks, venous thrombosis and pulmonary embolism, liver and breast tumors, cancer of the cervix, and disturbances in liver function (such as increased hepatic enzyme levels).

### Statistical Analysis

Based on the previous large-scale study with NGM/EE 0.25/0.035 mg, the rate of breakthrough bleeding is expected to decrease from 4.5% before use to 3% after 6 cycles, and the rate of intermenstrual spotting to decrease from 9% to 4% [17]. Therefore, a sample size of 175 participants would have 80% power to detect a treatment effect on breakthrough bleeding at a 1-sided α level of 5%. To account for a potential dropout rate of 30%, we plan to screen 240 women for eligibility and enroll 228 participants, an average of 38 participants at each of the 6 centers.

Two datasets have been defined for analysis: the per-protocol set, which includes all participants with full treatment adherence and no major protocol deviations, and the intention-to-treat set, which includes all enrolled participants who received at least 1 dose of NGM/EE 0.25/0.035 mg. The primary outcome will be evaluated only in the per-protocol population to avoid any effects of noncompliance on the interpretation of this outcome. However, secondary efficacy outcomes and safety will be assessed in the intention-to-treat population using robust statistical methods against missing data, like linear mixed models.

Continuous variables will be described using the mean and standard deviation if they are normally distributed or using the median and interquartile range if nonnormally distributed. The distribution of these variables will be assessed using the 2-tailed Student *t* test for paired data or the Wilcoxon signed rank test. Categorical variables will be described using frequencies and percentages and compared using the chi-square test or Fisher exact test [25]. There will be no imputation for missing data, and data from unscheduled visits will not be included in the analysis. No adjustment for multiplicity will be made to adjust for a type I error in secondary end points. A *P* value of .05 is considered to be statistically significant.

All statistical analyses will be performed using the R statistical software (version 3.5 or later; R Foundation for Statistical Computing). The final analysis will be completed after all participants have completed the study, any queries have been resolved, and the database has been locked.

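### The stated 80% power with 175 women cannot be obtained from the breakthrough bleeding rates given (4.5% to 3%), and no rate is given for the bleeding-or-spotting measure that is the primary end point

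*Protocol article*

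**What the plan says.** The Statistical Analysis section of the protocol article takes its planning rates from an earlier large-scale study. It expects that "the rate of breakthrough bleeding is expected to decrease from 4.5% before use to 3% after 6 cycles" and, as a separate item, "the rate of intermenstrual spotting to decrease from 9% to 4"%. It then draws the inference that "a sample size of 175 participants would have 80% power to detect a treatment effect on breakthrough bleeding", "at a 1-sided α level of 5"%. It names no formula, no within-woman correlation and no discordance rate.

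The End Points section uses the same term in a wider sense: "breakthrough bleeding (ie, bleeding or spotting between the cyclically regular onset of menses". Table 1 defines it in the same way. The primary measure is obtained by "calculating the intermenstrual bleeding or spotting occurrence rate at the sixth cycle and comparing this with the rate at baseline". Comparison to Prior Work again reports breakthrough bleeding and intermenstrual spotting as two separate rates.

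The study has one group, so baseline and cycle 6 are observed in the same women.

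**The concern.** The power sentence follows directly from a pair of rates labelled breakthrough bleeding, and those rates describe a small change in a rare event. In 175 women, 4.5% is 175 × 0.045 = 7.9 women and 3% is 175 × 0.03 = 5.3 women, a difference of 2.6. A contrast of that size cannot be detected with 80% probability at this sample size.

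This sentence is the only justification given for the sample size. If bleeding alone fell exactly as assumed, a non-significant result would still be the likelier outcome. A reader who trusted the 80% figure could then take that result as evidence against an effect. If the sentence was meant for bleeding or spotting together, the reader cannot check it, because the article gives no rate for that composite.

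**Working it through.** **Inputs.** From Statistical Analysis: N = 175, power 80%, one-sided α = 5%, breakthrough bleeding 4.5% to 3%, spotting 9% to 4%. From End Points: the same women are compared at baseline and cycle 6. The within-woman correlation φ is not given, so it is varied.

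**Formulas.** Let p0 and p1 be the baseline and cycle-6 rates and p11 the proportion of women with the event at both times.

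- p11 = p0·p1 + φ·√(p0(1−p0)·p1(1−p1)); p10 = p0 − p11; p01 = p1 − p11
- ψ = p10 + p01; d = p0 − p1
- McNemar N = (1.645·√ψ + 0.8416·√(ψ − d²))² / d²
- McNemar power at n = Φ[(d·√n − 1.645·√ψ) / √(ψ − d²)]

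**Attempt to reproduce 80% at 175 from 4.5% to 3%** (d = 0.015, d² = 0.000225).

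*No correlation.* p11 = 0.00135, p10 = 0.04365, p01 = 0.02865, ψ = 0.0723.
- N = (1.645 × 0.2689 + 0.8416 × 0.2685)² / 0.000225 = 1,985.
- Power at 175 = Φ[(0.1984 − 0.4423) / 0.2685] = Φ(−0.908) = 18%.

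*Full nesting* (every cycle-6 bleeder also bled at baseline, the most favourable case; φ = 0.81). p10 = 0.015, p01 = 0, ψ = 0.015.
- N = (1.645 × 0.1225 + 0.8416 × 0.1216)² / 0.000225 = about 410.
- Power at 175 = Φ[(0.1984 − 0.2014) / 0.1216] = Φ(−0.025) = 49%.
- The exact test does worse. Only 175 × 0.015 = 2.6 discordant women are expected, while one-sided significance needs at least five in the same direction (0.5⁵ = 0.031; 0.5⁴ = 0.0625). The exact power is 12.5%.

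| Method, 4.5% to 3%, one-sided 5% | Power at 175 | N for 80% |
|---|---|---|
| McNemar, φ = 0 | 18% | 1,985 |
| McNemar, φ = 0.2 | 21% | 1,596 |
| McNemar, φ = 0.4 | 24% | about 1,207 |
| McNemar, full nesting | 49% | about 410 |
| McNemar exact, φ = 0 up to full nesting | 12-14% | – |
| One-sample test against a fixed 4.5% | 20% | about 1,044 |
| Two independent groups of 175 | 18% | 1,983 per group |

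No variant comes near 80%. The smallest N is 410/175 = 2.3 times the stated one.

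**Can 175 arise from the wider definition?** The composite rate depends on how far bleeding and spotting occur in the same women, which the article does not say. The two ends used here are assumptions: full overlap gives 9% to 4%; no overlap gives 4.5 + 9 = 13.5% to 3 + 4 = 7%.

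- *13.5% to 7%, McNemar.* At φ = 0.37, p11 = 0.0417, p10 = 0.0933 and p01 = 0.0283, so N = 176.
- *13.5% to 7%, one-sample against a fixed 13.5%.* N = 143. With the null variance only, (1.645 + 0.8416)² × 0.135 × 0.865 / 0.065² = 171.
- *9% to 4%, one-sample against a fixed 9%.* N = 162.
- *Either end, McNemar at n = 175, φ from 0 to 0.4.* Power is about 60-84% when summed over the number of discordant pairs (60-81% by the closed formula), and higher with stronger correlation.

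So 175 is attainable for the composite, but each route needs a composite rate and either a correlation or a fixed reference rate that the article does not give.

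**The case against.** The strongest reply is that the article defines its term. End Points and Table 1 both say that breakthrough bleeding includes spotting, and the power sentence comes after both the bleeding and the spotting rates. On that reading the powered quantity is the primary end point, and 175 is a plausible number for it. This stands as far as it goes, and it rules out several stronger conclusions that a reader might draw.

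- *That the trial is powered for something other than its primary end point.* This is true only if the term is read narrowly. The article's own definition allows the other reading.
- *That only the spotting contrast comes near 175.* The non-overlapping composite does so too, at N = 176 or 171.
- *That 24% is a ceiling.* It is the value at correlation 0.4. Stronger correlation raises the asymptotic figure to about 49%.
- *That the trial is likely to miss on its primary end point.* The low power applies to bleeding alone. The composite figures are far more favourable.
- *That a one-sided calculation is paired with a two-sided analysis.* The sentence that a P "value of .05 is considered to be statistically significant" gives no direction, and the 2-tailed label is attached only to the paired t test. This is an ambiguity, and the analysis plan may settle it.

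The reply does not rescue the sentence as printed. The same paragraph attaches the name to the 4.5% and 3% rates and lists spotting separately, and the composite rate cannot be derived from the two component rates without an overlap assumption.

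**Conclusion.** The point holds in this form: the power statement is wrong on the only rates given under the name it uses. For 4.5% to 3% at one-sided 5%, 175 women give about 18-24% power (asymptotic McNemar, correlation 0 to 0.4), 12-14% with the exact test, and no more than about 49% under full nesting. Reaching 80% needs about 410 to 1,985 women in a paired test, or about 1,044 in a one-sample test. No value of the unstated correlation changes this conclusion.

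In addition, the End Points and Statistical Analysis sections use breakthrough bleeding in two senses, and the primary measure has no planning rate. The documents do not show that the primary end point is underpowered. They show that its power cannot be determined from what is printed. The composite figures above rest on assumed overlap and correlation and serve only as illustration.

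The statement should be corrected before the results are reported, because it governs how a non-significant finding will be read.

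**What to change.** 1. Withdraw the claim of 80% power for a fall from 4.5% to 3%.
2. Use breakthrough bleeding in one sense in both End Points and Statistical Analysis.
3. Restate power, or the expected precision, for the declared primary end point: any intermenstrual bleeding or spotting, cycle 6 versus baseline. Give the assumed composite rates, a paired test, the within-woman correlation or discordance, the evaluable number expected in the per-protocol set, and the same sidedness as the primary analysis. The sponsor should supply these assumptions; the illustrative figures here are not a substitute.
4. Label bleeding alone as descriptive.

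The cost is a change of wording in the sample-size paragraph and in any matching text of the analysis plan. The stated power may become less favourable. No extra participants are needed.

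### The sample size rests on a 1-sided 5% level, but the analysis text fixes no side for the primary categorical test, and the stated 80% power does not follow from 4.5% to 3% at either level

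*Protocol article*

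**What the plan says.** All the statistical statements are in the Statistical Analysis section of the protocol article.

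- **Planning.** The main assumption is that "the rate of breakthrough bleeding is expected to decrease from 4.5% before use to 3% after 6 cycles". For spotting, the assumed fall is from 9% to 4%. The article concludes that "a sample size of 175 participants would have 80% power to detect a treatment effect on breakthrough bleeding". The level for that calculation is set "at a 1-sided α level of 5" percent, and this is the only mention of a 1-sided level.
- **Analysis of continuous variables.** Two paired tests are named, Wilcoxon's and the t test, and the latter is introduced by "The distribution of these variables will be assessed using the 2-tailed Student". This is the only mention of sidedness in the analysis text.
- **Analysis of categorical variables.** They are "compared using the chi-square test or Fisher exact test", with no side given and no paired test named.
- **Threshold.** For all tests, a P "value of .05 is considered to be statistically significant", with no side given.

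The End Points section defines the primary measure by "calculating the intermenstrual bleeding or spotting occurrence rate at the sixth cycle and comparing this with the rate at baseline". That is a yes/no outcome seen twice in the same women, so the categorical sentence governs it.

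**The concern.** The planning sentence and the analysis text do not fix the same decision rule. A one-degree-of-freedom chi-square statistic squares the difference and so loses its direction; rejecting at .05 is a two-sided 5% rule. If that is how the primary test is read, the power was calculated for a more lenient rule than the one applied.

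Two things are at stake. First, the same data can be positive under one rule and negative under the other, and with a single primary comparison and no control group the choice could be made after the data are seen. Second, readers will take 80% as the power of the analysis that is run.

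**Working it through.** **1. The plan's own figure.** Inputs from Statistical Analysis: 4.5% to 3%, 80% power, 1-sided 5%, n = 175. The article gives no within-woman correlation, so I take the full range as an assumption, from independence to the maximum (no woman newly starts to bleed).

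Let p10 be the proportion bleeding at baseline only, p01 at cycle 6 only, D = p10 + p01 and d = p10 − p01 = 0.015. The McNemar normal approximation gives

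n = (z_α√D + z_β√(D − d²))² / d²

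- Independence: p10 = 0.045 × 0.97 = 0.04365, p01 = 0.03 × 0.955 = 0.02865, D = 0.0723. n = (1.645 × 0.2689 + 0.842 × 0.2685)² / 0.000225, about 1985.
- Maximum correlation: p10 = 0.015, p01 = 0, D = 0.015. n = (1.645 × 0.1225 + 0.842 × 0.1216)² / 0.000225, about 411.

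Treating the two occasions as independent samples gives 1983 per occasion. The figure of 175 is not reproduced.

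**2. Power with 175 women, 4.5% to 3%.** Power = Φ[(d√n − z_α√D) / √(D − d²)], with d√175 = 0.1984.

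| Within-woman correlation | 1-sided 5% | 2-sided 5% |
|---|---|---|
| Independence | Φ(−0.91) = 18% | Φ(−1.22) = 11% |
| Maximum | Φ(−0.02) = 49% | Φ(−0.34) = 37% |

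The bottom row is generous. It rests on 175 × 0.015 = 2.6 expected discordant women, where the normal approximation is poor. An exact 1-sided test needs at least 5 discordant women, all favourable (0.5⁵ = 0.031; 0.5⁴ = 0.063 is not enough). The chance of 5 or more under a binomial (175, 0.015) is about 12.5%.

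**3. Effect of sidedness alone.** Suppose 175 did give 80% at 1-sided 5%.

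- Power at 2-sided 5% = Φ(1.645 + 0.842 − 1.960) = Φ(0.527) = 70%.
- Sample ratio for 80% = ((1.960 + 0.842) / (1.645 + 0.842))² = 1.27. Unrounded, 1.2695 × 175 = 222.2, so 223 evaluable women.

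**4. Can the side decide the result?** As an illustration, take the expected spotting change at n = 175: 9% is 15.75, rounded to 16 women, and 4% is 7 women. With the tests the article names, treating the occasions as independent:

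- chi-square: P = .052 uncorrected, .084 with continuity correction;
- Fisher: P = .082 two-sided, .041 one-sided.

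Spotting is only one component of the primary outcome, but a result close to the sponsor's expectation passes the 1-sided rule and fails the two-sided one.

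**The case against.** A reader might infer that the article says the primary test is two-sided and so contradicts its own sample size outright. It does not say that. The term 2-tailed belongs to the t test for continuous variables; the categorical sentence and the .05 threshold have no side. Fisher's test has a standard one-sided form, and a one-degree-of-freedom chi-square has a directional equivalent in its signed root. A one-sided P below .05 would satisfy both the planning sentence and the threshold. This part of the objection stands: the mismatch is the usual reading of a chi-square test at .05, not a stated rule.

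A reader might also infer that sidedness explains the power shortfall. It does not. For 4.5% to 3%, power is far below 80% even one-sided, and the drop from 80% to 70% is conditional on an 80% that those rates do not deliver.

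A fair defence of the 80% is that the End Points section counts spotting as breakthrough bleeding, so the calculation may have meant another rate. Adding the two rates (13.5% to 7%, assuming no overlap) gives 64-96% one-sided and 51-93% two-sided by the same approximation. Some unreported correlation would then yield 80%. But the article does not say that this was done, and on that reading the side matters more, because the 80% would be tied to the 1-sided level.

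Finally, an article may leave detail to a fuller protocol or analysis plan, and the mention of chi-square could cover McNemar's version. That lowers the weight of what is unsaid. It does not remove the point, because the article itself states a level, a power and a threshold that do not fix one rule.

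**Conclusion.** The point holds as a failure to fix the primary decision rule, together with a stated power that the stated rates do not support. The 1-sided 5% level appears only in the sample size sentence. Read in the usual way, a chi-square test at .05 is two-sided, which would turn a true 80% into about 70% and leave results with a favourable two-sided P between .05 and .10 open to either conclusion.

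The larger numerical gap is separate from sidedness: 18-49% one-sided or 11-37% two-sided for 4.5% to 3% with 175 women. Those ranges rest on a normal approximation and on an assumed correlation; the upper ends are optimistic.

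**What to change.** Before database lock:

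1. State one level and side for the primary test and use it in both the sample size and the analysis text. Either 2-sided .05 with a 95% confidence interval for the change, or 1-sided .05 with the matching 90% interval, would resolve the point; the choice is the sponsor's.
2. Name a paired test (McNemar) for baseline against cycle 6, since the same women are compared.
3. Restate the power of the planned number for that test, giving the rate it refers to and the within-woman correlation assumed.

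The cost is a few sentences in the protocol and analysis plan. No new participants or data are needed. The stated power becomes less favourable.

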**Methods:**

This is a prospective observational study being undertaken in a target population of 228 healthy Italian women aged 18-35 years who are starting oral contraception for the first time or switching from another COC. The participants are asked to complete a diary for 6 cycles recording information about their menstrual cycles (frequency, duration, regularity, estimated flow volume, and breakthrough bleeding), any unscheduled bleeding, and an evaluation of dysmenorrhea, using a 100-mm visual analog scale from 0=no pain to 100=very severe pain, and any adverse events. Compliance is assessed after 3 and 6 months via returned medication. The primary end point is the change from baseline in the rate of intermenstrual bleeding during the sixth cycle. At baseline, 3 months, and 6 months, acne will also be assessed using the Global Acne Grading Scale, and participants will complete a Profile of Mood State to assess premenstrual syndrome and the Female Sexual Function Index to evaluate the quality of their sex life. A subgroup of 28 participants at 1 site (Genoa) is also providing a blood sample for the assessment of metabolic, endocrine, and coagulation parameters.

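### Enrolling 228 does not cover 30% dropout from 175: it leaves about 160 evaluable women, and 175 remain only if loss is at most about 23%

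*Protocol article*

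**What the plan says.** All the figures stand in the Statistical Analysis section of the protocol article.

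- **Required size.** A sample of 175 "would have 80% power to detect a treatment effect on breakthrough bleeding" at a one-sided 5% level.
- **Expected rates.** The section says that "the rate of breakthrough bleeding is expected to decrease from 4.5% before use to 3% after 6 cycles", and separately expects intermenstrual spotting to fall from 9% to 4%.
- **Allowance for loss.** "To account for a potential dropout rate of 30%, we plan to screen 240 women for eligibility and enroll 228 participants", an average of 38 at each of 6 centres (6 × 38 = 228). The Methods paragraph of the Abstract repeats the target: "undertaken in a target population of 228 healthy Italian women aged 18-35 years".
- **Analysis set.** The primary outcome is analysed in the per-protocol set alone, which requires full adherence and no major deviations. Missing data are not imputed. Mixed models are named for secondary efficacy outcomes and safety only.
- **Endpoint.** The End Points section compares the intermenstrual bleeding or spotting rate at the sixth cycle with the baseline rate.

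**The concern.** The text presents 228 as the enrolment that protects 175 evaluable women against 30% dropout. A dropout rate is a share of those enrolled, so the enrolled number must be the required number divided by the share who stay. The figure 228 looks instead like the required number with 30% of itself added, which always falls short.

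The sample-size statement is the plan's justification for its enrolment target. As written, a reader would believe that 175 evaluable women and 80% power are secured even if 30% leave. If the inflation is wrong, neither is secured under the plan's own assumption. Because a woman who leaves before the sixth cycle has no primary outcome, is not imputed and is outside the per-protocol set, nothing in the primary analysis recovers the loss.

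**Working it through.** **Inputs (Statistical Analysis section).** Required n = 175; power 80%; one-sided α = 5%; dropout d = 30%; screened 240; enrolled 228.

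**1. Reproduce the plan's figure.**
- n × (1 + d) = 175 × 1.30 = 227.5, rounded up to 228. This matches exactly.
- n / (1 − d) = 175 / 0.70 = 250. This does not match; the difference is 250 − 228 = 22 women.

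**2. Check in the other direction.**
- Evaluable at 30% dropout: 228 × 0.70 = 159.6, about 160.
- Shortfall: 175 − 160 = 15 women, or 15/175 = 8.6%.
- Largest loss that still leaves 175: 1 − 175/228 = 23.2%.
- Taking the 30% off those screened instead: 240 × 0.70 = 168, still below 175.

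**3. Effect on power, with 80% at 175 taken at face value.** Under a normal approximation the standardised effect scales with √n.
- At 175: z(0.95) + z(0.80) = 1.645 + 0.842 = 2.486.
- At 159.6: 2.486 × √(159.6/175) = 2.486 × 0.955 = 2.374.
- Power: Φ(2.374 − 1.645) = Φ(0.730) = 76.7%, about 77%.

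**4. Effect on power for the spotting rates, paired comparison.** With p₁ = 0.09, p₂ = 0.04, δ = 0.05 and within-woman correlation ρ:
- p₁₁ = p₁p₂ + ρ√[p₁(1−p₁)p₂(1−p₂)], and the discordant proportion is ψ = p₁ + p₂ − 2p₁₁.
- Power = Φ{[δ√n − 1.645√ψ] / √(ψ − δ²)} (McNemar, normal approximation).

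The document gives no correlation; 0 to 0.4 is an assumption.

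| ρ | ψ | Power at 175 | Power at 160 |
|---|---|---|---|
| 0 | 0.1228 | 59.7% | 56.4% |
| 0.4 | 0.0779 | 76.9% | 73.6% |

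The ranges are therefore about 60–77% at 175 and 56–74% at 160. The loss is again about 3 points. The rates 9% and 4% are for spotting alone; the endpoint covers bleeding or spotting, and the article gives no expected rate for the combination.

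**The case against.** **The loss is small and the 30% is only a potential rate.** This stands. It is a planning allowance, 175 is still reached if loss is 23% or less, and the power cost is about 3 points. If the 9% baseline is treated as a known constant (a one-sample test), 160 women still give about 79.5%. That reading ignores the sampling error in the women's own baseline, but it shows that the shortfall alone does not sink the study. It limits the severity; it does not make 228 right.

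**Perhaps the 30% was meant differently.** Counted relative to completers, 228 − 175 = 53 losses is 53/175 = 30%. But 53 of 228 enrolled is 23%, and a reader will take a dropout rate as a share of those enrolled. Applying it to the 240 screened does not help either.

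**A reader might infer that per-protocol exclusions come on top of the 30%.** The article does not define dropout, and the allowance could have been meant to include non-adherence and major deviations. What can be said is that losses from the per-protocol set may exceed dropout alone.

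**A reader might infer that enrolling 250 would secure 80% power.** The document does not support that. The 250 corrects the inflation step and takes 175 as given. Whether 175 follows from the stated rates is a separate matter: for 4.5% to 3%, the same paired formula at 175 gives about 18% power with independent responses and about 49% in the most favourable case, where no woman newly starts bleeding.

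**Conclusion.** The point holds. Within one section, a requirement of 175, a dropout rate of 30% and an enrolment of 228 cannot all be true. Under the stated rate, 228 leaves about 160 evaluable women, 15 short (8.6%), and the figure offered is in fact an allowance for about 23% loss. These results need only the printed numbers and the usual meaning of a dropout rate.

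The power cost is about 3 points: 80% to about 77% if the plan's claim for 175 is accepted, with a similar drop for the spotting rates under the assumed correlations. It is a clear but modest planning error that should be fixed. It does not show that the trial must enrol more women, since the inconsistency can be removed by restating the figures.

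**What to change.** Keep 228 enrolled and correct the sentence in the Statistical Analysis section in one of two ways:

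- state that 228 enrolled gives about 160 evaluable women at 30% dropout, and recompute the power at 160; or
- state that 175 evaluable women from 228 enrolled assumes at most 23% dropout.

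Either version should also say whether the allowance is meant to cover exclusions from the per-protocol set as well as withdrawal. The 228 in the Abstract can stand.

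The cost is wording and one short calculation. No enrolment, procedure or analysis changes; the stated evaluable number and power, or the tolerated dropout, become slightly less favourable. If 175 is itself recalculated, the new figure should be divided by 0.70, not multiplied by 1.30, for as long as 30% dropout is assumed.

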### Comparison to Prior Work

The previous large-scale study conducted in Germany among 59,701 women evaluated 342,348 menstrual cycles and showed a reduction in breakthrough bleeding from 4.5% at baseline to 3% during cycle 6 of the COC and in intermenstrual spotting from 9% to 4% during cycle 6 [16]. In the Italian study by Affinito et al [18], in which 92 women received monophasic NGM/EE, the incidence of breakthrough bleeding decreased from 3.3% to 0% at cycle 6, and the rate of spotting from 14.3% to 3.7%. Our study will include at least twice the number of women as in the earlier Italian study and therefore a more robust assessment of the effects of NGM/EE on these menstrual characteristics.

The large German study highlighted the extremely high contraceptive efficacy of NGM/EE, showing a use-efficacy Pearl index of 0.25 (95% CI 0.19-0.31) pregnancies per 100 woman-years [17], and no pregnancies were reported in the earlier Italian study [18]. There was a low incidence of AEs and a high rate of compliance in both these analyses [17,18]. Our study will provide updated information on the contraceptive efficacy, adherence rate, and safety or tolerability profile of NGM/EE 0.25/0.035 mg. The substudy is investigating the effect of NGM/EE 0.25/0.035 mg on lipid and metabolic parameters, expected to be negligible based on previous research [17,18].

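### The 80% power is stated for 175 women and inflated for dropout alone, but the primary outcome is analysed per protocol only; 30% off 228 leaves about 160 even before any further per-protocol exclusion

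*Protocol article*

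**What the plan says.** Everything that matters here is in the Statistical Analysis section of the protocol article, apart from the adherence measure.

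- Target: "a sample size of 175 participants would have 80% power to detect a treatment effect on breakthrough bleeding", with a one-sided 5% test. The effect named is that "the rate of breakthrough bleeding is expected to decrease from 4.5% before use to 3% after 6 cycles".
- Inflation: "To account for a potential dropout rate of 30%, we plan to screen 240 women for eligibility and enroll 228 participants". No other loss is mentioned.
- Analysis set: "The primary outcome will be evaluated only in the per-protocol population", defined as "the per-protocol set, which includes all participants with full treatment adherence and no major protocol deviations". The reason given is to keep noncompliance from affecting the result. Missing data are not imputed.
- Adherence measure (End Points section): "Adherence is being evaluated as a percentage of tablets taken, based on the medication returned by participants at each visit". No percentage is given for what counts as full.

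**The concern.** A power statement should refer to the number of women who enter the analysis. Here the number is adjusted for one kind of loss, while the primary set is formed by three conditions: sixth-cycle data must exist, adherence must be full, and there must be no major deviation. Under Procedures, early withdrawal is described as leaving before the end of the sixth cycle. A woman who completes the cycle but missed tablets has not withdrawn, yet she is removed from the only set in which the primary outcome is evaluated.

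At stake is whether 175 is a number the plan can be expected to analyse. If it is not, the primary comparison has less power and a wider confidence interval than the article leads a reader to expect.

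**Working it through.** **Inputs from the article:** 175 women, 80% power, one-sided 5%, 30% dropout, 228 enrolled, 240 screened. **Not in the article:** f, the share of completers who are fully adherent and free of major deviations. It is an assumption throughout.

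**1. The plan's own enrolment figure.** 175 x 1.30 = 227.5, which rounds up to 228. So 228 comes from adding 30% to the target. Dividing by the share retained gives 175 / 0.70 = 250.

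**2. What 228 yields if dropout covers every exclusion (f = 100%).** 228 x 0.70 = 159.6, about 160, or 15 short of 175. Taking 30% off the 240 screened would leave only 168. The largest total loss that 228 can bear is 1 - 175/228 = 53/228 = 23.2%, less than the 30% the plan itself names. With 30% dropout, f would have to be 175/159.6 = 110% to reach 175, which is impossible.

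**3. What 228 yields if some completers are also excluded.** Analysed N = 228 x 0.70 x f.

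**4. Relative loss of power.** Take the plan's 80% at 175 as given and change only N. The noncentrality at 175 is z(0.95) + z(0.80) = 1.645 + 0.842 = 2.487, so power(N) = Phi(2.487 x sqrt(N/175) - 1.645).

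| f (assumed) | Analysed N | Power, if 175 gave 80% |
|---|---|---|
| 100% | 159.6, about 160 | 77% |
| 95% | 151.6, about 152 | 75% |
| 90% | 143.6, about 144 | 73% |
| 80% | 127.7, about 128 | 68% |
| 70% | 111.7, about 112 | 63% |

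**5. Why the last column shows only relative loss.** The 80% at 175 could not be reproduced for a fall from 4.5% to 3% at one-sided 5%. At n = 175, a one-sample normal test gives 20% power. A McNemar test gives 18% if the two occasions are independent, and 49% under the most favourable pairing (all discordant pairs in one direction). The table therefore shows how a claimed 80% erodes as N falls, not what power the trial has.

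**The case against.** The strongest reply is that the only shortfall the article proves is the one in step 2, and that this comes from how 30% was applied to 175, not from the per-protocol filter. That is right. The further loss is a matter of principle in the article, and its size depends wholly on f. The article does not define dropout, so 30% may have been meant as total loss to the primary analysis. That reading removes the second loss but still leaves about 160. Nor is 175 out of reach in practice: it would be met if total loss turned out at 23% or less. For example, 15% dropout would need f of at least 175 / (228 x 0.85) = 90%.

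Three stronger readings are tempting and are not supported.

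- A reader might infer that one missed tablet in six cycles excludes a woman, so that the per-protocol set will be very small. The article gives no cut-off, and the percentage measure under End Points fits a threshold set in the full protocol or analysis plan. The Comparison to Prior Work section reports high compliance in both earlier studies. It gives no figure, and high average compliance is not the same as full adherence, so it fixes f in neither direction.
- A reader might infer that the trial has, say, 68% power. Step 5 shows why that does not follow.
- A reader might infer that the Discussion is wrong to say "Our study will include at least twice the number of women as in the earlier Italian study and therefore a more robust assessment", since 2 x 92 = 184 exceeds 175. The sentence compares women included with the 92 who received the product in the earlier study, and 228 exceeds 184. It is true as written.

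The adherence filter also has a stated rationale. Relaxing it would change what the primary analysis estimates and is not part of this point.

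**Conclusion.** The point holds in a limited form. The article states power for 175 women, allows for dropout only, and analyses a narrower set. On its own figures the analysed number is about 160 at most when 30% are lost, and lower by the factor f if completers are also excluded. The shortfall of 15 women needs no assumption beyond the plan's own 30%; anything beyond it rests on f, which the documents do not give. On the plan's own terms, the isolated effect of the per-protocol filter is modest if f is high (77% to 73% at f = 90%) and larger if f is low (77% to 63% at f = 70%). The derivation of 175 is a separate and larger question. Correcting it, or the dropout arithmetic, would still leave the per-protocol loss unnamed.

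**What to change.** Restate the size sentence in the Statistical Analysis section for the set actually analysed:

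- Give the expected per-protocol number as 228 x (1 - dropout) x (assumed share of completers who are adherent and free of major deviations), with both assumptions stated.
- Report the power or the confidence-interval width at that number, in place of the figure for 175.
- State which percentage of tablets taken the plan means by full adherence, so that the share can be estimated. The value is for the sponsor to state.

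This is a change of wording and needs no extra enrolment, visits or data. The cost is a less favourable stated power. It discloses the smaller number and does not restore 175; at 30% dropout, restoring it would take 250 enrolled at f = 100%, or 175 / (0.70 x 0.90) = 278 at f = 90%.
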